## 9. Efficacy Analysis

### 9.1. Primary analysis

The primary analysis will be conducted on an intention-to-treat basis using a proportional odds model (ordinal logistic regression) with an assumed common odds ratio of improvement on the mRS. We will test whether the proportional odds assumption is satisfied using chi square test. A secondary analysis will use an additive multivariable model adjusting for all the minimization variables included as co-variables. Only main effects will therefore be considered in this model. The results will be expressed as an odds ratio with 95% confidence limits. Additional analyses will include a safety population analysis defined to include only those patients who

received an interventional procedure, an on-protocol analysis including those patients who were treated according to protocol. If the proportional odds assumption is not satisfied we will revert to a binary outcome of independence (mRS 0-2) vs. dependence or death (mRS 3-6) at 90 days. This will be assessed using a Fisher's exact test.

The primary analysis will be unadjusted. Because the randomization is being balanced a priori according to key prognostic variables (age, sex, NIHSS, ASPECTS, occlusion location and tPA use), we expect that the unadjusted analysis will be similar to the adjusted analysis.

A revised statistical analysis plan may be modified according to the statistical distribution of variables and finalized prior to breaking the blind.

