## 6. Randomization

Randomization will be managed using a custom SQL server-based database that will instantly and dynamically assign treatment using the minimal sufficient balance algorithm. Randomization will therefore be conducted over the internet via a desktop computer or a web-enabled smart phone.

Randomization will be 1:1. Allocation will be 1:1 set at  $p(0.5)$  for the first 40 patients. Thereafter, a minimization algorithm (minimal sufficient balance) will be utilized to ensure ongoing balance in the trial on the following factors:

- Age

- Baseline NIHSS score

- Sex (male or female)

- Baseline ASPECTS score, dichotomized as 6-7 or 8-10.

- Intracranial occlusion location, dichotomized as MCA or ICA.

- IV tPA use (yes or no)

The minimal sufficient balance (MSB) randomization is a minimization procedure that preserves balance in smaller trials, such as this one, where imbalances in important baseline prognostic variables may occur by chance and confound the primary outcome. In addition, it preserves a greater degree of randomness in patient allocation compared to permuted block designs. Because of the MSB process, randomization assignments will be stochastically derived in real time using a interactive web-site and therefore concealment can never be breached. Allocation will be open.

Reliance on a process that requires real-time data entry makes the process susceptible to error. For example, incorrect information (eg. wrong sex or incorrect site of occlusion) could be mistakenly entered into the randomization process and affect the minimization algorithm. Post-hoc, when such errors become known, the quality-controlled database entry will be considered the source of truth and the randomization database will be updated to ensure that ongoing randomization utilizes the most correct data to determine balance in an ongoing way.

The randomization process is not blocked, nor stratified by site. Therefore, the number of patients enrolled into each arm of the study may not be exactly even at the time the study is completed. The proportion of patients enrolled into each arm at each site may also vary and not be equally distributed. These decisions were taken explicitly with the knowledge and belief that balance on 6 key patient characteristics in the trial overall are more important than balance by site.

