## 9.2. Secondary analyses

Pre-specified secondary outcome and safety analyses of proportions will be conducted in a similar way to the primary analysis using logistic regression or using a multivariable generalized linear model with log link to derive risk ratios directly. Pre-specified secondary analyses will include the following:

- 9.2.1. Adjusted analysis on the primary outcome using key stratifying variables from the MSB algorithm (age, sex, tPA use, ASPECTS score, NIHSS score, occlusion location)
- 9.2.2. Adjusted analysis using other known predictors of outcome after stroke (6 variables above, time, serum glucose, atrial fibrillation, ipsilateral carotid artery stenosis/occlusion, diabetes mellitus, blood pressure at baseline, miFUNCTION score)
- 9.2.3. Dichotomized outcome on the 90-day: mRS (independent 0-2 vs. dependent 3-6), the NIHSS 0-2 vs. 2-42, Barthel index 95-100 vs. 0-90, mortality. Each dichotomized outcome will be modeled as a function of key covariates (as per 8.2.2) using logistic regression model. The odds ratio and the corresponding 95% confidence interval for each covariate will be reported
- 9.2.4. Reperfusion and recanalization analysis based upon angiographic data (endovascular group) and CTA data (control group). Proportion of patients with early recanalization, extent of recanalization.
- 9.2.5. Analysis of the role that time from onset and time from CT imaging plays in predicting outcome defined by the mRS by group.
- 9.2.6. Analysis on the primary outcome using baseline imaging as a stratifying variable (ASPECTS 8-10 vs. 5-7, multi-phase CTA collaterals good vs. intermediate and perfusion CT small vs. intermediate infarct core) Simple effects and interactions will be considered in this analysis.
- 9.2.7. Analysis of quality of life, measured using the EuroQOL. We will report the unadjusted distribution by group.
- 9.2.8. Economic analysis will be conducted using Canadian hospital data and quality of life measure to estimate treatment utility.

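### Balance from minimisation does not justify an unadjusted primary analysis: if the six factors are prognostic, the test is conservative and forgoes power that the planned adjusted model would give

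*SAP*

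**What the plan says.** Section 9.1 sets the primary analysis as intention-to-treat, "using a proportional odds model (ordinal logistic regression) with an assumed common odds ratio of improvement on the mRS". It then states: "The primary analysis will be unadjusted. Because the randomization is being balanced a priori according to key prognostic variables", naming age, sex, NIHSS, ASPECTS, occlusion location and tPA use, and concludes that "we expect that the unadjusted analysis will be similar to the adjusted analysis".

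Adjustment is planned, but only as secondary. Section 9.1 says "A secondary analysis will use an additive multivariable model adjusting for all the minimization variables included as co-variables", and item 9.2.1 repeats it: "Adjusted analysis on the primary outcome using key stratifying variables from the MSB algorithm".

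Section 6 allocates the first 40 patients with probability 0.5. "Thereafter, a minimization algorithm (minimal sufficient balance) will be utilized to ensure ongoing balance in the trial on the following factors", and the same six factors follow. It justifies the method by the risk that "imbalances in important baseline prognostic variables may occur by chance and confound the primary outcome". The plan therefore treats the factors as prognostic, without saying how strongly.

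Section 3 sizes the trial at 188 per group for 90% power at a common odds ratio of 1.8, using Whitehead's formula and no covariates.

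**The concern.** The plan uses balance as a reason not to adjust. Two things follow from balancing on prognostic factors, and neither makes the two analyses alike.

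- **Standard error.** Forced balance removes part of the real sampling variation of the treatment estimate. The unadjusted model still computes its standard error as if allocation had been simple randomisation. That standard error is too large and the test is conservative.
- **Odds ratio.** In a proportional odds model, the odds ratio conditional on prognostic covariates lies further from 1 than the marginal one, even under perfect balance. The two estimates should therefore be expected to differ.

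Both effects grow with prognostic strength, which is the property that Section 6 gives as the reason for minimising. At stake is power that costs no patients, because the six variables must be known before allocation.

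**Working it through.** **1. The plan's own figure.** For 1:1 allocation, Whitehead's total is N = 12(z₀.₉₇₅ + z₀.₉₀)² / [ln(OR)² (1 − Σp̄³)]. The projected mRS distribution is in Figure 1, which is not shown, so six equal categories (mRS 5 and 6 combined) are assumed.

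- (1.960 + 1.282)² = 10.507; ln(1.8)² = 0.3455; 1 − 6 × (1/6)³ = 0.9722.
- N = 12 × 10.507 / (0.3455 × 0.9722) = 375.4, or 188 per group, as stated.
- 376 / (1 − 0.06) = 400, as stated. Calculated power at 376 is 90.0%.

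Two moderately skewed distributions give 190 and 191 per group. One with 40% in category 5–6 gives 197.

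**2. Simulation inputs.**

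- From the SAP: 376 patients, six outcome categories, six factors (age and NIHSS continuous, four binary), first 40 patients at probability 0.5, two-sided 0.05.
- Assumed, because the SAP does not give them: an imbalance vote at p < 0.3; a biased coin of 0.65 (0.90 as a check); prevalences of 0.5, 0.25, 0.3 and 0.7 for the binary factors; equal outcome categories; and a linear predictor with SD s of 0.5, 1.0 or 1.5.
- Latent R² = s²/(s² + 3.29), which gives 0.07, 0.23 and 0.41.
- Replicates: 4000 under the null with coin 0.65, 3000 under the null with coin 0.90, and 2000 for power. Monte Carlo standard error is √(0.05 × 0.95/4000) = 0.34 points for size and √(0.9 × 0.1/2000) = 0.67 points for power.

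**3. Results under the null (coin 0.65 unless stated).**

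| Latent R² | Unadjusted model SE | Actual SD of estimate | Type I error, unadjusted | Type I error, adjusted | Unadjusted, coin 0.90 |
|---|---|---|---|---|---|
| 0.07 | 0.182 | 0.180 | 4.5% | 5.3% | 4.7% |
| 0.23 | 0.182 | 0.170 | 3.8% | 5.5% | 3.4% |
| 0.41 | 0.182 | 0.159 | 2.4% | 4.8% | 2.6% |

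As a cross-check, the size implied by a standard error that is too large is 2[1 − Φ(1.96 × SE/SD)]. The arguments are 1.96 × 0.182/0.180 = 1.98, 1.96 × 0.182/0.170 = 2.10 and 1.96 × 0.182/0.159 = 2.24, which give 4.8, 3.6 and 2.5%. These agree with the simulated sizes.

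**4. Results with the marginal odds ratio held at about 1.8 (coin 0.65).**

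| Latent R² | Power, unadjusted | Power, adjusted | OR, unadjusted | OR, adjusted |
|---|---|---|---|---|
| 0.07 | 88.9% | 91.3% | 1.78 | 1.84 |
| 0.23 | 88.3% | 95.2% | 1.77 | 1.98 |
| 0.41 | 90.5% | 98.8% | 1.77 | 2.21 |

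The power forgone is about 2, 7 and 8 points. The unadjusted test stays near its planned 90%, and the adjusted test exceeds it.

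**The case against.** **The planned test does what it was sized to do.** A reader might infer that the trial is underpowered. If 1.8 were the odds ratio conditional on the six factors, a smaller simulation with the factors explaining 10, 20 and 30% of latent variance puts unadjusted power at 88, 82 and 75%. The documents do not support that reading. Section 3 derives 1.8 from projected outcome distributions by arm, uses an unadjusted formula and says that covariates were not considered, so 1.8 is a marginal odds ratio. On that scale unadjusted power is 88 to 90%. This objection stands: what is lost is power beyond the target.

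**The error is on the safe side.** A reader might also take an incorrect standard error to mean an invalid test. It does not, because type I error falls below 5%. This stands too.

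**The marginal odds ratio is a legitimate target, and the factors are not ignored.** Both are true. The adjusted model is prespecified as secondary, and marginal and conditional odds ratios answer different questions. But Section 9.1 does not argue for the marginal quantity. It argues that balance makes the choice immaterial, and that is the part that fails.

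**The size is uncertain.** With weak factors the gain is only about 2 points. The direction is secure, but the size depends on inputs the SAP does not give.

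**Changing the model has consequences elsewhere in the plan.** Section 9.1 makes the ordinal analysis conditional on a test of proportional odds, with a dichotomised Fisher's exact fallback. Section 6 gives precedence to quality-controlled covariate values. Section 8 leaves the imputation of missing covariates open. A bare swap of the two analyses would handle none of these, so the fix has to.

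**Conclusion.** The point holds as one of efficiency and of an incorrect justification, not of validity. If the six factors are prognostic, balance makes the unadjusted test conservative (type I error about 4.5% down to 2.4%) and leaves about 2 to 8 points of power unused. The adjusted odds ratio also lies further from 1: 1.84 to 2.21 against 1.77 to 1.78.

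The sizes rest on assumed allocation parameters, factor prevalences, outcome distribution and a latent R² between 0.07 and 0.41. A much tighter coin changes the type I error figures little. The stated sample size and 90% power reproduce for the unadjusted test under a roughly even outcome distribution.

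**What to change.** - Make the proportional odds model with treatment and the six minimisation factors the primary analysis. Enter age and NIHSS as continuous, and sex, ASPECTS stratum, occlusion site and IV tPA as binary. Use the quality-controlled values to which Section 6 gives precedence.
- Report the unadjusted common odds ratio as supportive. State that the primary odds ratio is conditional on the factors and tends to lie further from 1.
- Apply the proportional odds check to the treatment term only, so that a violation by a covariate such as age or NIHSS does not trigger the dichotomised fallback.
- Adjust that fallback for the same six factors, for example by logistic regression for mRS 0–2 in place of Fisher's exact test.
- Fix one imputation rule for missing covariate values, replacing the open choice in Section 8.
- Delete the balance argument from Section 9.1.

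All of this should be settled before unblinding, which Section 9.1 allows. It needs no extra patients, and the six variables are already used for allocation. The cost is SAP wording, a primary odds ratio with a conditional interpretation, and a fixed rule for missing covariates.

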## 9.2. Secondary analyses

Pre-specified secondary outcome and safety analyses of proportions will be conducted in a similar way to the primary analysis using logistic regression or using a multivariable generalized linear model with log link to derive risk ratios directly. Pre-specified secondary analyses will include the following:

- 9.2.1. Adjusted analysis on the primary outcome using key stratifying variables from the MSB algorithm (age, sex, tPA use, ASPECTS score, NIHSS score, occlusion location)
- 9.2.2. Adjusted analysis using other known predictors of outcome after stroke (6 variables above, time, serum glucose, atrial fibrillation, ipsilateral carotid artery stenosis/occlusion, diabetes mellitus, blood pressure at baseline, miFUNCTION score)
- 9.2.3. Dichotomized outcome on the 90-day: mRS (independent 0-2 vs. dependent 3-6), the NIHSS 0-2 vs. 2-42, Barthel index 95-100 vs. 0-90, mortality. Each dichotomized outcome will be modeled as a function of key covariates (as per 8.2.2) using logistic regression model. The odds ratio and the corresponding 95% confidence interval for each covariate will be reported
- 9.2.4. Reperfusion and recanalization analysis based upon angiographic data (endovascular group) and CTA data (control group). Proportion of patients with early recanalization, extent of recanalization.
- 9.2.5. Analysis of the role that time from onset and time from CT imaging plays in predicting outcome defined by the mRS by group.
- 9.2.6. Analysis on the primary outcome using baseline imaging as a stratifying variable (ASPECTS 8-10 vs. 5-7, multi-phase CTA collaterals good vs. intermediate and perfusion CT small vs. intermediate infarct core) Simple effects and interactions will be considered in this analysis.
- 9.2.7. Analysis of quality of life, measured using the EuroQOL. We will report the unadjusted distribution by group.
- 9.2.8. Economic analysis will be conducted using Canadian hospital data and quality of life measure to estimate treatment utility.

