## 8. Missing data

Under the ITT principle, all patients who are randomized are included in the analysis. Therefore, missing data, especially in the outcome measures, can be problematic. Thus every effort will be made to keep all missing data to a minimum. In the event that, despite the clinical centers' best efforts, there are missing data, then for the primary outcome analysis, missing outcome data will be imputed by assuming the missing mRS score at 3 months to be unfavorable. We will assign the worst possible score. If the patient is known to be alive, we will impute a score of 5. If the patient is not known to be alive or dead, we will impute a score of 6.

Furthermore, if the assessment was conducted outside of the protocol-specified time window, data obtained are still included in the analysis, with the rationale that it is a more accurate measure than those obtained by imputation. At a minimum 90-day outcome assessments will be accepted within a +/- 30-day window.

For sensitivity analysis, the missing outcome values will be imputed using the following methods:

- If one-month or 5-day/discharge outcome scores are available, carry forward those values; else, assume the worst case.
- Assign failure (worst possible score) to all subjects with missing 3-month outcome data.
- Multiple imputation method based on the regression model
- Hot-deck or nearest neighbor method, using clinical site, age, sex, baseline NIHSS, baseline serum glucose, baseline ASPECTS, IV tPA use, treatment group as classification variables.
- Regression method, with age, sex, baseline NIHSS, baseline serum glucose, IV tPA vs. non-IV tPA, and treatment group as covariates.
- In the endovascular group, impute values for LTFU with failure (worst possible score), and in the control group, with success (the best-worst case imputation) in the intervention group.

Similar imputation methods will be employed for secondary categorical outcomes. For the raw NIHSS score, multiple imputation, regression, and mean substitution methods will be used in the sensitivity analyses. Missing covariate data, if any, will be imputed using either multiple imputation or regression method, if needed.

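### SAP 9.2.3 puts a 90-day NIHSS score of 2 in both outcome categories, so this secondary endpoint cannot be coded as written; its covariate cross-reference is also stale

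*SAP*

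**What the plan says.** Section 9.2.3 lists the dichotomised 90-day outcomes. The first is "mRS (independent 0-2 vs. dependent 3-6"; the list continues with "the NIHSS 0-2 vs. 2-42, Barthel index 95-100 vs. 0-90, mortality".

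The same item then gives one model for all of them: "Each dichotomized outcome will be modeled as a function of key covariates (as per 8.2.2) using logistic regression model". It adds that an odds ratio and 95% confidence interval will be reported for each covariate.

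Two covariate lists stand just above it. Section 9.2.1 uses the "key stratifying variables from the MSB algorithm (age, sex, tPA use, ASPECTS score, NIHSS score, occlusion location"). Section 9.2.2 uses other known predictors, listed as "6 variables above, time, serum glucose, atrial fibrillation, ipsilateral carotid artery stenosis/occlusion, diabetes mellitus, blood pressure at baseline, miFUNCTION score". The section that carries the number 8 is "8. Missing data", and it has no numbered subsections.

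**The concern.** A binary endpoint needs two categories that do not overlap and together cover the scale. The NIHSS split fails the first requirement: a patient who scores 2 is both a success and a failure. In practice a program would give that patient to whichever condition it tests first, so the endpoint would be settled by coding order and not by the plan.

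The text does not show which half holds the slip. If the first half is right, success is 0-2; if the second half is right, success is 0-1. These are different thresholds for a pre-specified secondary efficacy outcome.

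The covariate reference is a lesser matter of the same kind. It points to a section that is not there, and its number and its wording suggest different lists. Because every covariate's odds ratio is to be reported, the list determines both the adjustment and what is published.

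**Working it through.** The plan states no figure on this point that could be reproduced. The check is one of set membership, section numbers and counts.

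**Step 1: the splits in 9.2.3.** For each, take the two categories A and B on the scale S. The overlap is A ∩ B, and the gap is what remains of S outside A ∪ B.

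| Outcome | Scale | A | B | Overlap | Gap |
|---|---|---|---|---|---|
| mRS | 0-6 | 0-2 | 3-6 | none | none |
| NIHSS as written | 0-42 | 0-2 | 2-42 | {2} | none |
| Barthel | 0-100 in steps of 5 (step assumed) | 95-100 | 0-90 | none | none |

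Mortality is binary by nature. Only the NIHSS split is faulty.

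**Step 2: the possible repairs.**

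- 0-2 vs 3-42: no overlap, no gap. It keeps the first half of the text.
- 0-1 vs 2-42: no overlap, no gap. It keeps the second half.

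The two differ only in where a score of 2 goes. No other section gives the NIHSS cut, so the SAP does not decide between them.

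**Step 3: how many patients this could touch.** The SAP gives no distribution of 90-day NIHSS scores. Assume that 3-8% of patients score exactly 2:

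- With 400 patients (Section 3): 0.03 × 400 = 12 to 0.08 × 400 = 32.
- With the maximum of 500 (Section 3): 0.03 × 500 = 15 to 0.08 × 500 = 40.

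Nothing in the SAP shows how these patients would divide between the arms, so the effect on the odds ratio cannot be worked out.

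**Step 4: the covariate reference.**

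- 8.2.2 does not exist, since Section 8 has no numbered subsections.
- 9.2.1 has 6 variables: age, sex, tPA use, ASPECTS, NIHSS and occlusion location.
- 9.2.2 has 6 + 7 = 13: those six plus time, glucose, atrial fibrillation, carotid disease, diabetes, blood pressure and the miFUNCTION score.
- For 9.2.2: the last two digits match, efficacy is now Section 9, and the item stands directly above the sentence.
- For 9.2.1: the adjective in 9.2.3 is the one that 9.2.1 uses. Sections 6 and 9.1 also attach it to the six minimisation factors.

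The number is the stronger evidence, so 9.2.2 is the likelier reading, but the wording leaves some doubt.

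**The case against.** The strongest reply is that both are slips in secondary analyses and that the plan has a way to mend them. Section 9.1 allows the SAP to be revised and finalised before the blind is broken. That stands, and it limits the consequence. It does not remove the point, because the NIHSS cut appears only once and the slip does not reveal the intended value.

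Three stronger readings are tempting, and the document does not support them.

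- *A reader might infer that none of the 9.2.3 analyses can be run.* The mRS, Barthel and mortality outcomes are well defined. Their only obstacle is a section number that very probably means 9.2.2.
- *A reader might infer that the six variables of 9.2.1 must be used, because 13 would over-fit mortality.* The SAP gives no mortality rate. At an assumed 15-20% of 400, there are 60-80 deaths. Treatment plus 13 covariates then gives 60/14 = 4.3 to 80/14 = 5.7 events per parameter, against 60/7 = 8.6 to 80/7 = 11.4 with six. At 500 patients there are 75-100 deaths, giving 75/14 = 5.4 to 100/14 = 7.1, against 75/7 = 10.7 to 100/7 = 14.3. This is a reason for the sponsor to think about the mortality model. It is not evidence of what was intended, and it concerns one of four outcomes.
- *A reader might infer that the choices will be made with results in hand, because treatment is open-label.* Section 9.1 provides for finalising earlier, and Section 7 has the 90-day assessment done by someone outside the acute treatment. The interim efficacy statistic in Section 4 is an unadjusted comparison of mRS 0-2, and the DSMB steps listed there call on neither the NIHSS split nor the 9.2.3 models. The risk arises only if the line is left uncorrected.

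**Conclusion.** The NIHSS dichotomy in 9.2.3 is wrong as written. It classifies one score, 2, both ways, and the SAP offers no means of resolving it. This finding needs no assumption. The number of patients affected does: 12-32 of 400, or 15-40 of 500, rests on an assumed 3-8% scoring exactly 2.

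The reference to 8.2.2 is a minor accompanying error. It most likely means the 13 variables of 9.2.2, but it should be confirmed, not presumed.

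The consequence stays within the secondary analyses. The unadjusted ordinal primary analysis, its binary fallback, the adjusted analysis in 9.2.1 and the interim test do not depend on either error.

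**What to change.** In 9.2.3, state one non-overlapping NIHSS cut before unblinding: 0-2 vs 3-42 if 0-2 is the intended success category, which matches the first half of the present text, or otherwise 0-1 vs 2-42.

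In the same item, replace the reference to 8.2.2 with the correct section number and name the intended covariate set, either the 13 variables of 9.2.2 or the 6 of 9.2.1. The sponsor should record which was meant; this review does not choose between them.

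The cost is two small edits to one SAP item, through the revision route that Section 9.1 already provides. No change to sample size, data collection or the primary analysis is needed.
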